## **SUMMARY**

### **Background:**

Mechanical ventilation (MV) is associated with increased morbidity and associated complications increase with the duration of respiratory support. Weaning period is a difficult time and represents 40% of the total duration of mechanical ventilation. The aim is to reduce duration of MV while minimizing the risk of extubation failure. Automated systems seem useful to reduce the duration of weaning but cannot anticipate extubation failure itself. Despite standardization, weaning from MV has a failure rate around 30-35%. Extubation failure, and the need for reventilation during the 48 hours-period following extubation, are clearly associated with increased mortality and morbidity. In a patient being ventilated for more than 48 hours and presenting criteria for extubability, a spontaneous breathing trial (SBT) is conducted in order to approach support-free ventilatory conditions. Arterial blood gases, plasma BNP and echocardiography are proposed to adapt PaO2, monitor PaCO2 or detect cardiac dysfunction. SBT success test allows extubation of the patient.

Our clinical study is designed to evaluate lung ultrasound, echocardiography and plasma BNP levels during the weaning period, in order to assess the relationship between these parameters and SBT or extubation failure. Thus, expected loss of lung aeration during clinical failure could be attributed to cardiac causes. These results could lead to assess prospectively SBT and extubation failures in ICU patients.

### **Objectives:**

#### **Main objective:**

To compare the changes in pulmonary aeration during SBT (before, at the end, and 4-6 h after) between patients requiring reventilation before the 48th hour, and those weaned permanently.

#### **Secondary objectives:**

- Studying variations, during weaning from mechanical ventilation, of pressure of left ventricle filling (E / Ea) coupled with those of plasma BNP.
- Assessing the effects of E / Ea and BNP variations on the success or failure in the 4-6 early hours.
- Compare the variations of a lung ultrasound score during the test of the weaning from mechanical ventilation between patients failed the spontaneous breathing test (SBT) and those extubated after successful SBT.

**Type of study:** Biomedical, prospective, observational, open, nonrandomized.

**Description of the study:**

The eligibility of patients is sought every morning by the ICU medical staff. Patients meeting inclusion criteria are included, after giving their consent or the consent of next of kin.

The measurements are performed in three steps:

- Blood withdrawal before SBT
- At the end of SBT
- After extubation in case of success to SBT

Before and at the end of SBT (1 hour of pressure support ventilation, PSV), we analyze arterial blood gases, BNP plasma levels, and we perform lung and cardiac echography. In case of SBT success, the patient is extubated and arterial blood gases, BNP levels and lung and cardiac ultrasound are evaluated again between H4 and H6.

Patients are followed until the 48th hour after extubation, and patients are then considered as definitely weaned if they need less than 9L/min of oxygen support while breathing spontaneously in order to maintain pulse oximetry above 95%, if they do not need non invasive ventilation (NIV) and if they do not need reintubation.

**Primary endpoint:**

The primary endpoint is based on the assessment of a pulmonary aeration score (*Lung Ultrasound Score*) before/after SBT, and after extubation.

**Secondary endpoints:**

The secondary evaluation criteria based on:

- pulmonary aeration score
- left ventricular filling pressure (as determined by cardiac ultrasound)
- plasma BNP levels

**Estimated number of patients:** 100

**Inclusion criteria:**

- Age  $\geq 18$  years
- Duration of mechanical ventilation  $> 48$  hours
- Indwelling arterial catheter
- Patient considered stable under PSV
  - o pressure support  $\leq 8$  cmH2O - PEEP  $\leq 5$  cmH2O - FiO2  $\leq 40\%$  - Spo2  $\geq 95\%$  - Respiratory Rate (RR)  $\leq 20$ /min
  - Tidal volume (Vt)  $> 7$  ml/kg of ideal body weight
  - o Glasgow Coma Scale  $\geq 13$  and interruption of sedation
  - o Body temperature  $< 38^{\circ}\text{C}$
  - o No vasopressor support and a systolic blood pressure (SBP)  $< 160$  and  $> 100$  mmHg.
- Informed consent from the patient (or from next of kin if the patient is not able to speak)
- Patient under French Social Security system.

**Exclusion criteria:**

- Refusal of the patient or his designated person of trust
- Tracheotomy
- Trauma with spinal paraplegia above T8 level
- Cardiac arrhythmias (atrial fibrillation) or electrostimulation
- Absence of patient echogenicity at the thoracic level

**Benefits and risks of this study:**

No risk is expected for enrolled patients. Medical devices used in the study (e.g. ventilators, echography) are widely used in clinical practice. Expected benefits consist in the improvement of knowledge in predicting extubation failure.

**LIST OF ABBREVIATIONS**

AI: Pressure Support Ventilation

BNP: Brain Natriuretic Peptide

FC: Heart Rate

FiO2: Fraction of Inspired Oxygen

FR: Respiratory

GDS: From Blood Gas

ITV: Full-time speed

OAP: Acute Pulmonary Edema

PaCO2: Blood Pressure CO2

NOT: Systolic Blood Pressure

PEP: Positive Expiratory Pressure

SpO2 Oxygen Saturation

VG: Left Ventricle

NIV: Non-Invasive Ventilation

VS: Spontaneous Ventilation

### ***13 Communication - Publishing Rules***

### ***14 List of appendices***

### ***15 Bibliography***

## **1 Rationale of the study:**

Weaning from mechanical ventilation is a critical period in intensive care unit (ICU) patients (1, 2). Weaning failure includes initial spontaneous breathing trial (SBT) failure, postextubation distress and death occurring within 48h following extubation (1). Postextubation distress is defined as reintubation or need for non-invasive ventilation within 48 hours following extubation (1, 3). Following a successful SBT, incidence of reintubation ranges between 3 and 30% (1, 3). Postextubation distress after a successful SBT is associated with increased morbidity and mortality (4). Given the risks associated with delayed or unsuccessful extubation, determining readiness for extubation and predicting postextubation distress is a critical challenge in the ICU. Most of proposed predictors of postextubation distress either require special equipment, or are too complex for bedside use, or have a limited predictive value (3). To date, there are no simple clinical indices known to be powerful predictors of postextubation distress. Many mechanisms may impact on the ability to wean from mechanical ventilation, including spontaneous breathing-induced cardiac failure, and neuromuscular disorders, or alteration of lung resistance and compliance.

### **1.1 Current Practice of weaning from mechanical ventilation**

SBT is performed in patients with all the requirements (SpO2 of 90% or higher under FiO2 less than 40% and positive expiratory pressure (PEEP) of 5 cmH2O or under, hemodynamic stability, Ramsay score of 3 or less, minimal or interrupted sedation, presence of cough, need for less than three tracheal aspirations during the last four hours, no planned procedure requiring sedation or planned surgical intervention).

SBT is run on a T-tube for 1 hour, in order to mimic the conditions under which the patient will be found once extubated. Arterial blood gases, plasma BNP levels and echocardiography may be assessed in order to adapt the level of O2, to monitor PaCO2 monitor or to detect cardiac dysfunction. SBT success (RR <35/min, no chest indrawing, SpO2> 90% with maximal FiO2 of 50% or 9L/min of O2, HR <120 bpm or change in HR<20%, SBP <200mmHg or >80 mmHg, absence of drowsiness or agitation) allows extubation. Following extubation, arterial blood gases, BNP levels and/or echocardiography may help to monitor tolerance.

### **1.2 Ultrasound lung and withdrawal**

The causes of failure of extubation are multiple and sometimes result from complex pathophysiology, including changes in respiratory, cardiac, neuromuscular, metabolic, nutritional, and psychological states. The final alteration in gas exchanges leading to reventilation could be a consequence of a loss in lung aeration. Pulmonary aeration and its variation can be quantified at the bedside by lung ultrasound, a reproducible and non-invasive technique. This technique also helps to assess the type of pulmonary subpleural areas (alveolar or interstitial edema, consolidation, bronchopneumonia images, pleural effusions...). An ultrasound score has been proposed to quantify pulmonary vascular extracellular water (10-16). A significant loss of lung ultrasound aeration could predict SBT failure. In case of SBT success, lung aeration could also predict the need for reventilation.

### **1.3 Cardiac evaluation during weaning**

Cardiogenic pulmonary edema (CPE) is a recognized cause of SBT failure. Mechanical ventilation profoundly alters cardiorespiratory interactions. SBT is associated with the return to a regime of negative intrathoracic pressures that increases venous blood return to the heart. As a result, increased left ventricular preload, as well as afterload, can lead to increased myocardial work. It increases especially because of increased work of breathing and increased sympathetic activity, partly due to anxiety. This phenomenon can lead to CPE-related

hemodynamic dysfunction when left ventricular systolic preexists. However, worsening of diastolic dysfunction alone and variations in left ventricular filling pressures (E/Ea) are not described during SBT. The E / Ea ratio is the ratio of the velocity of diastolic filling of the LV blood pulsed Doppler mitral velocity on displacement of the mitral annulus by pulsed Doppler tissue. BNP (Brain Natriuretic Peptide) is a measurable peptide hormone secreted by cardiac ventricles in response to an increase in ventricular wall stress. This marker is used in clinical practice for the diagnosis of dyspnea resulting from CPE (19). BNP is a reliable marker of left ventricular dysfunction left and its plasma concentrations are correlated to the pressure level of filling (19). BNP monitoring during weaning from MV could be useful to better predict extubation failure (1, 20, 21).

#### **1.4 Summary of the benefits and risks of the research:**

No risk is expected for enrolled patients. Medical devices used in the study (e.g. ventilators, echography) are widely used in clinical practice. Expected benefits consist in the improvement of knowledge in predicting extubation failure.

#### **1.5 Goals and potential interests of our project:**

Our clinical study is designed to evaluate lung ultrasound, echocardiography and plasma BNP levels during the weaning period, in order to assess the relationship between these parameters and SBT or extubation failure. Thus, expected loss of lung aeration during clinical failure could be attributed to cardiac causes. These results could lead to assess prospectively SBT and extubation failures in ICU patients.

## **2 Objectives**

### **2.1 Principal objective**

To compare the changes in pulmonary aeration during SBT (before, at the end, and 4-6 h after) between patients requiring reventilation before the 48th hour, and those weaned permanently.

### **2.2 Secondary objectives**

- Studying variations, during weaning from mechanical ventilation, of pressure of left ventricle filling (E / Ea) coupled with those of plasma BNP.
- Assessing the effects of E / Ea and BNP variations on the success or failure in the 4-6 early hours.
- Compare the variations of a lung ultrasound score during the test of the weaning from mechanical ventilation between patients failed the spontaneous breathing test (SBT) and those extubated after successful SBT.

### 3 Description of the study

#### 3.1 Type of study

This is a biomedical research (RBM), prospective, open, non-randomized, two-center, study.

#### 3.2 Evaluation criteria

##### 3.2.1 Primary Outcome

The primary endpoint is the assessment of lung aeration scores Pulmonary (*Lung Ultrasound Score*) test before and after SBT, and after extubation. We will use the lung aeration score proposed and validated by [name] (16). No additional mobilization of the patient is necessary. Each thoracic quadrant is scanned in its entirety by the ultrasound probe, and points are attributed: 0 points = Ventilation normal lung sliding single or "N"; 1 = tails of comets spaced "B1"; 2 = tails comets curtains "B2"; Consolidation 3 = "C". The score is an average score obtained at each phase of weaning. We will also evaluate the variation of aeration in its entirety.

[figure not shown]

##### 3.2.2 Secondary endpoints:

The secondary evaluation criteria include:

- The lung aeration score, as described in the previous paragraph
- The LV filling pressure (cardiac ultrasound)
- The plasma BNP levels
- Criteria for echocardiography:
  - o Diameter of chamber hunting VG
  - o Kinetics segmental
  - o FRS%
  - o ITV subaortic
  - o mitral pulsed Doppler blood flow: E wave, TDE, A wave
  - o Doppler tissue ring: Ea lateral
  - o ITVmax

##### 4.1 Procedure protocol

At inclusion, patient demographics, clinical, ventilatory and hemodynamic data are collected (see book collection in the appendix section).

Before SBT, we analyze arterial blood gases, plasma BNP levels, and we perform cardiac and lung echography.

At the end of SBT, we again analyze arterial blood gases, plasma BNP levels and cardiac/lung echography.

Blood sample is gathered from an indwelling arterial catheter, allowing both arterial blood gases analysis and measurements of BNP blood levels.

Echography is a noninvasive technique and is totally harmless to the patient. The use of ultrasound in intensive care is part of routine clinical practice, including weaning period, used to optimize patient management. Echography completion time is around 5 to 10 minutes per patient. The same doctor will perform all ultrasound evaluations at each center: [name] [name] in Clermont-Ferrand and [name] [name] at Pitié-Salpêtrière Hospital.

In case of SBT success, the patient is extubated and analysis of blood gases, BNP levels assessment and cardiac/lung echography are performed at H4-6.

Patients are followed until the 48th hour after extubation, and are considered as finally weaned in the absence of the need for oxygen therapy above 9L/min to maintain  $SpO_2 > 95\%$ , in the absence of the need for non-invasive or invasive reventilation (NIV or reintubation).

SBT failure criteria and reventilation criteria:

- $RR > 35/\text{min}$
- Chest indrawing
- $SpO_2 < 90\%$  under  $FiO_2$  of 50% or higher, or under  $O_2$  therapy flow  $> 9\text{L}/\text{min}$
- $HR > 120\text{ bpm}$  or change in  $HR > 20\%$
- $SBP > 200\text{ mmHg}$  or  $< 80\text{ mmHg}$
- Agitation
- Drowsiness

Extubation failure criteria: failure of extubation is an event defined at H48 post-extubation by:

- The need for NIV\*:
  - o the need for more than 3 hours of NIV per day after abdominal or thoracic surgery
  - o in a hypercapnic COPD patient
- $O_2\text{ mask} > 9\text{ l} / \text{min}$  for a  $SpO_2 > 92\%$ ;

- Clinical signs of respiratory distress: RR > 35/min, SpO2 < 90% under O2 > 9L/min, circulation, exhaustion, poor hemodynamic tolerance, HR > 120, SBP > 160 or < 90 mmHg, or poor tolerance with neurological agitation, impaired consciousness;
- The need for reintubation;
- Death within 48 hours after extubation.

*\* In these situations “prophylactic” NIV is probably advisable (grade 2, consensus conference on NIV; 2006 SRLF-SFAR-SPLF).*

The diagram of the course of study is in Appendix 1.

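### The 48-hour success and failure definitions are not complements, so some extubated patients fit neither primary group and a few could fit both

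*Protocol*

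**What the plan says.** **Success.** Section 4.1 has patients "considered as finally weaned in the absence of the need for oxygen therapy above 9L/min to maintain" an SpO2 above 95%, and "in the absence of the need for non-invasive or invasive reventilation (NIV or reintubation"). The Summary (Description of the study) gives the same idea in other words: patients are weaned "if they need less than 9L/min of oxygen support while breathing spontaneously in order to maintain pulse oximetry above 95" per cent, with no NIV and no reintubation.

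**Failure.** The extubation failure list in section 4.1 has five items:
- need for NIV, with two sub-items: "the need for more than 3 hours of NIV per day after abdominal or thoracic surgery" and "in a hypercapnic COPD patient";
- mask oxygen above 9 L/min for SpO2 above 92%;
- clinical signs of respiratory distress, among them RR above 35 and "exhaustion, poor hemodynamic tolerance, HR > 120, SBP > 160 or < 90 mmHg";
- reintubation;
- death within 48 hours.

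A footnote to the NIV item says that prophylactic NIV is probably advisable in these situations.

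**Reventilation criteria.** A further list in section 4.1 serves both SBT failure and reventilation. Its systolic limits are above 200 or below 80 mmHg.

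**Labels.** Section 2.1 compares changes in lung aeration "between patients requiring reventilation before the 48th hour, and those weaned permanently". Section 6.1 counts patients with and without extubation failure at 48 hours. Section 6.2 tests *weaning failure* against *successful weaning* and does not say which definition applies.

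**The concern.** A two-group comparison needs a rule that puts every analysed patient in exactly one group. Here success and failure are written independently, with different oxygen conditions, different treatment of NIV and different components. The result decides who enters each arm of the primary test in section 6.2. It is also evidently the outcome against which the ROC curves for the lung ultrasound score are drawn.

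The study runs in two centres. Where the text leaves a patient unassigned or allows two readings, the centres can code identical courses differently, or the choice can be made after the ultrasound data are known.

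**Working it through.** **The plan's own figures.** Inputs from section 6.1: 100 patients, 15% SBT failure, 35% extubation failure among those who pass.
- Passing SBT: 100 × (1 − 0.15) = 85.
- Failing extubation: 85 × 0.35 = 29.75, about 30.
- Not failing: 85 − 29.75 = 55.25, about 55.

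The arithmetic is right. It also shows that section 6.1 treats the groups as complements, since 30 + 55 = 85 leaves nobody over.

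**The two definitions side by side (section 4.1).**

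| Component | Success requires | Failure is met by |
|---|---|---|
| Oxygen | no need above 9 L/min for SpO2 > 95% | above 9 L/min for SpO2 > 92% |
| NIV | no need for NIV | > 3 h/day after abdominal or thoracic surgery; hypercapnic COPD |
| Clinical signs | not mentioned | RR, SpO2, HR, SBP and others |
| Reintubation | none needed | needed |
| Death | not mentioned | within 48 h |

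Only reintubation is the same in both columns.

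**Patient profiles, otherwise unremarkable, under the written rules.**

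| Profile | Weaned? | Failed? |
|---|---|---|
| 10 L/min needed for > 95%, 8 L/min enough for > 92%, no NIV | no | no |
| NIV 2 h/day after abdominal surgery | no | no |
| Prophylactic NIV 2 h/day in hypercapnic COPD | no, if all NIV counts | yes by the list; unclear given the footnote |
| SBP 170 alone, no support | yes | yes, on one reading |

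The first two profiles are gaps, and the third is an ambiguity. The fourth is a possible overlap: 170 lies beyond the failure list's 160 but within the reventilation list's 200, and the success sentence has no pressure limit.

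There is also a boundary mismatch. At exactly 9 L/min the Summary's condition (less than 9) is not met, but the condition in section 4.1 (not above 9) is.

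**Labels against content.** A patient who needs 12 L/min of mask oxygen for SpO2 above 92%, without NIV or reintubation, is an extubation failure under section 4.1. That patient has not been reventilated as section 2.1 words it. The patient on NIV 2 h/day after surgery is the reverse: ventilated again, but not a listed failure.

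The term *weaning failure* used in section 6.2 is defined only in section 1, where it also takes in SBT failure. Section 6.1 shows that this cannot be meant for the primary comparison, because its 30 and 55 are both drawn from the 85 who passed SBT. Section 6.2 does not say so.

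**The case against.** The strongest reply is that section 6.1 already supplies the complement: patients failing extubation against patients without extubation failure. On that view the failure list governs and the weaned sentence is only descriptive. This is a sensible way out, but section 6.2 does not adopt it, and sections 2.1 and 4.1 each put a separately worded success or failure group beside it.

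Several stronger readings are tempting and are not supported.

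- *The systolic limits contradict each other outright.* The 200/80 limits serve SBT failure and reventilation, and the 160/90 limits serve the 48-hour outcome. Different purposes can have different limits. The 160/90 limits also stand inside an item on signs of respiratory distress, so an isolated SBP of 170 need not count as failure.
- *Many patients fall in both groups.* Success turns on the absence of a need for reventilation, and the reventilation criteria include RR above 35 and HR above 120. A patient with RR 38 is therefore arguably not weaned. Coding a patient who died as weaned is a strained reading. Overlap is thus narrow.
- *Therapeutic NIV outside surgery and COPD escapes failure.* Most signs that would prompt it are in the clinical-signs item already; isolated chest indrawing or a heart-rate change above 20% are the exceptions. The sub-items may also be meant to qualify a general NIV rule.
- *The objective in section 2.1 defines a different group.* It may be shorthand for section 4.1, which makes this a wording mismatch.

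None of these replies removes the oxygen gap, the gap for short postoperative NIV, or the uncertainty about NIV in hypercapnic COPD.

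**Conclusion.** The point stands as an internal inconsistency in the primary grouping variable. Two gaps are certain on the text: oxygen need between the 95% and 92% conditions, and NIV of 3 hours or less a day after abdominal or thoracic surgery. The status of NIV in hypercapnic COPD is undetermined. Overlap is possible but depends on how the clinical-signs item is read. The failure group carries different labels in sections 2.1, 6.1 and 6.2.

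A reader might go on to infer a number of misclassified patients or a loss of power. The documents give neither the share of patients affected nor an expected difference or standard deviation for the score, so no such figure is claimed. For scale only, one reclassified patient is 1/85 = 1.2% of the extubated patients and 1/30 = 3.3% of the planned failure group.

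The text needs correction because the primary groups cannot be assigned reproducibly as written.

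**What to change.** Reconcile the passages into one definition of failure at 48 hours and define success as its exact complement among extubated patients, as the 30/55 split in section 6.1 implies. Use that definition, under one label, in the Summary and in sections 2.1, 4.1, 6.1 and 6.2.

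The definition should settle:
- the oxygen and SpO2 condition, including exactly 9 L/min;
- which NIV counts, and whether prophylactic NIV does;
- whether a single abnormal sign suffices or must accompany respiratory distress;
- that the reventilation criteria are separate from the research outcome, if that is intended.

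The clinical values are for the investigators to decide. Record each component separately in the CRF so that every assignment can be traced.

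The cost is protocol wording and a few CRF fields, with no extra patients or procedures.
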